## Abstract

**Background:**

Asymptomatic and symptomatic malaria during pregnancy has consequences for both mother and her offspring. Unfortunately, there is insufficient information on the safety and efficacy of most antimalarials in pregnancy. Indeed, clinical trials assessing antimalarial treatments systematically exclude pregnancy for fear of teratogenicity and embryotoxicity. The little available information originates from South East Asia while in sub-Saharan Africa such information is still limited and needs to be provided.

**Design:**

A Phase 3, non-inferiority, multicentre, randomized, open-label clinical trial on safety and efficacy of 4 ACT when administered during pregnancy was carried out in 4 African countries: Burkina Faso, Ghana, Malawi and Zambia. This is a four arm trial using a balanced incomplete block design. Pregnant women diagnosed with malaria are randomised to receive either amodiaquine-artesunate (AQ-AS), dihydroartemisinin-piperaquine (DHA-PQ), artemether-lumefantrine (AL), or mefloquine-artesunate (MQAS). They are actively followed up until day 63 post-treatment and then monthly until 4–6 weeks post-delivery. The offspring is visited at the time of the first birthday. The primary endpoint is treatment failure (PCR adjusted) at day 63 and safety profiles. Secondary endpoints included PCR unadjusted treatment failure up to day 63, gametocyte carriage, Hb changes, placenta malaria, mean birth weight and low birth weight. The primary statistical analysis will use the combined data from all 4 centres, with adjustment for any centre effects, using an additive model for the response rates. This will allow the assessment of all 6 possible pair-wise treatment comparisons using all available data.

**Discussion:**

The strength of this trial is the involvement of several African countries, increasing the generalisability of the results. In addition, it assesses most ACTs currently available, determining their relative ‘-value-’ compared to others. The balanced incomplete block design was chosen because using all 4-arms in each site would have increased complexity in terms of implementation. Excluding HIV-positive pregnant women on antiretroviral drugs may be seen as a limitation because of the possible interactions between antiretroviral and antimalarial treatments. Nevertheless, the results of this trial will provide the evidence base for the formulation of malaria treatment policy for pregnant women in sub-Saharan Africa.

**Trial registration:**

NCT00852423

## Background and rationale

The risk of malaria is higher in pregnant women than in the general population. There is insufficient information on the safety and efficacy of most antimalarial drugs in pregnancy [1] as they are systematically excluded from clinical trials for fear of teratogenicity and embryotoxicity [2]. This has complicated the generation of evidence-based recommendations for the prevention and treatment of malaria during pregnancy. Though the experience on the use of ACTs and their safety and efficacy in pregnancy is increasing (over 1,000 documented pregnancies, mainly in South East Asia), such information is still limited in sub-Saharan Africa [3]. Preclinical data indicate that the artemisinin derivatives were embryotoxic and potentially teratogenic in several animal species, without maternal toxic effects or impaired fertility [2]. More recent studies confirm these findings. One important aspect is that the critical window for drug exposure is approximately 10–14 days in the rat and their extrapolation to humans would indicate a sensitive period of weeks 2–6 of pregnancy [2]. There is increasing experience with the use of artemisinin derivatives in the second and third trimesters and there have been no reported adverse effects on the mother or foetus [4]. Despite limited data the World Health Organization (WHO) recommends effective artemisinin-based combination treatments (ACT) in the second and the third trimester and several African countries are already implementing it [3].

We propose to assess the efficacy and safety of the most important ACTs currently available, namely artemether-lumefantrine (AL), amodiaquine-artesunate (AQ-AS), mefloquine-artesunate (MQ-AS) and dihydroartemisinin-piperaquine (DHA-PQ). The choice of ACTs is based on several criteria, including known treatment efficacy in children, safety in pivotal phase-3 trials in children and adults, practicality of the dosing regimen (duration, e.g. 3 vs. 7 days), fixed dose combinations, drug tolerance, current availability in the population and affordable cost. The rationale for contemporaneously testing several drug regimens is to shorten the time of data collection and determine the relative ‘value’ of each treatment, providing the basis for an informed choice by malaria control programmes and policy makers.

Reliable data on the safety and efficacy of ACTs in pregnant women can be rapidly collected only within the context of a randomized-controlled trial. The production of such a large dataset will advance considerably the knowledge on the treatment of malaria in pregnancy in a relatively short period of time compared to pregnancy registers. One of the major issues for this trial is the altered pharmacokinetic of antimalarial drugs during pregnancy and the influence on the outcome of treatment. There has been a recent increase in trials that measure the pharmacokinetics of antimalarial drugs in pregnant women [5]. Recent information on the pharmacokinetics of both artemisinins [6] and partner drugs in the ACT is reassuring as amodiaquine [7], mefloquine [8] and piperaquine [9] do not seem to need dose adjustment. Nevertheless, the pharmacokinetic of lumefantrine (when administered as co-formulated artemether-lumefantrine) seems altered in pregnancy [10]. The clinical implications of the PK findings may not be clear from small rich PK studies alone and, unless the effects are important, may not be apparent in a pilot study in one site. Therefore, the proposed study aims not only at collecting safety and efficacy data on ACTs in a systematic and standardized manner but also explanatory variables (pharmacokinetic and *in vitro* drug sensitivity) that may help in interpreting the observed results.

ACTs have been shown to be extremely efficacious in children [11]. Efficacy is determined by the drug partnering the artemisinin derivative and, for artesunate–mefloquine, artemether–lumefantrine, and dihydroartemisinin–piperaquine, this usually exceeds 95% [12]. Amodiaquine-artesunate has proved to be an efficacious combination (range 90-95%) in areas where 28-day cure rates with amodiaquine monotherapy exceed 80% [13]. Few data on pregnant women are available but efficacy should be as good, if not better, than in children. In all the three areas where AQAS is assessed, efficacy of AQ monotherapy exceeds 80%. Therefore, it is expected that all the four treatments will have an efficacy of about 95%.

### Trial objectives and purpose

The main objective of the trial is to determine the safety and efficacy of 4 ACTs when administered to pregnant women with *P. falciparum* infection during the second and the third trimester, and collect explanatory variables for therapeutic response. The primary hypothesis is the clinical equivalence (pair-wise non-inferiority) of the 4 treatment regimens, with clinical equivalence defined as difference in treatment failure rates (PCR corrected) of 5% or less.

Specific objectives are:

to compare the efficacy of AL, AQ-AS, MQ-AS and DHA-PQ in terms of treatment failure by 63 days after start of treatment with or without genotyping; Parasite clearance time; Haematological recovery by 14, 28, 42 and 63 days post-treatment and at delivery; Birth weight measured within 72 hours of delivery; and prevalence of placenta *P. falciparum* malaria;to describe the safety profile of AL, AQ-AS, MQ-AS and DHA-PQ in terms of tolerability; incidence of adverse events until one year post-partum;to determine the relation between drug pharmacokinetics (Day 7 levels of the partner drug) and response to treatment;to assess the *in vitro* susceptibility of *P. falciparum* isolates collected before treatment to several drugs, including the partner drug tested, and to correlate their IC_50_ to treatment response.

### Trial design

#### Study design

This is a non-inferiority, multicentre, randomized, open label study on 4 antimalarial treatments, namely DHA-PQ, MQAS, AQAS and AL, assessed in each site using a “balanced incomplete block design” – with 3 out of 4 arms used in each site. There are 7 sites in the study distributed in the four countries, i.e. Burkina Faso (Nanoro and Nazoanga), Ghana (Effiduase, Ejisu and Juaben), Malawi (Chikwawa) and Zambia (Nchelenge).

The treatments tested are distributed in a way to allow a head-to-head comparison and the establishment of the treatment’s relative value according to a series of outcomes (Table 1). This approach has the advantage of testing several treatment options at the same time, maximizing the use of resources, and is the most likely to achieve our aim of identifying at least 2 antimalarial treatments suitable for use in pregnancy and one rescue/alternative treatment.

**Table 1 Tab1:** **Treatment arms per country/ site (number of patients)**

***West Africa: comparator AQAS***			
Burkina (870)	AL (290)	AQAS (290)	MQAS (290)
Ghana (870)	AQAS (290)	MQAS (290)	DHA-PQ (290)
***Eastern-Southern Africa: comparator AL***			
Malawi (870)	DHA-PQ (290)	AL (290)	AQAS (290)
Zambia (870)	MQAS (290)	DHA-PQ (290)	AL (290)

AQAS: amodiaquine-artesunate; DHA-PQ: dihydroartemisinin-piperaquine; AL: artemether-lumefantrine; MQAS: Mefloquine-artesunate.

The primary analysis is the assessment of therapeutic equivalence of the 4 treatments (clinical non-inferiority) with respect to therapeutic success at day 63 and their safety throughout the follow up, i.e. up to one year after delivery.

The following procedures are used to ensure an unbiased assignment of treatment safety and efficacy:The randomization list is generated prior to the beginning of the study.The interpretation of the PCR reading is blinded or masked with regard to the treatment allocation of the patients.An independent Data Safety and Monitoring Board (DSMB) reviews all safety data.

#### Primary endpoint

There are two primary end points:**Treatment Failure** (TF) (PCR adjusted) at day 63 defined according to the WHO criteria [14] as the sum of early and late treatment failures. Early Treatment Failure (ETF) could be one of the following: Development of danger signs or severe malaria on Day 0, Day 1, Day 2 or Day 3, in the presence of parasitaemia; Parasite density on Day 2 > Day 0 count, irrespective of axillary temperature; Presence of parasitaemia on Day 3 with fever (axillary temperature ≥ 37.5°C); Parasitaemia on Day 3 ≥ 25% of count on Day 0. Late treatment failure (LTF) is divided in late clinical and late parasitological failure. Late Clinical Failure (LCF): Development of danger signs or severe malaria on any day after Day 3 in the presence of parasitaemia, without previously meeting any of the criteria of Early Treatment Failure; Presence of parasitaemia and fever on any day after Day 3, without having previously meet the criteria of ETF. Late Parasitological Failure (LPF): Presence of parasitaemia on any day from day 7 onwards and axillary temperature <37.5°C, without previously meeting any of the criteria of ETF or LCF. The Adequate Clinical and Parasitological Response (ACPR) is 1-TF. It is defined as absence of parasitaemia at the end of the follow up period, irrespective of axillary temperature without previously meeting any of the criteria of early and late treatment failure. In the adjusted estimates, patients with late asexual parasite reappearance (with or without fever) are considered ACPR if the PCR analysis shows a new infection rather than a recrudescence.**Safety profiles** including significant changes in relevant laboratory values. Subjects are monitored for 63 days for possible development of adverse events. All adverse events are recorded on the specific form in the electronic CRF. Vital signs, blood chemistry and haematology are monitored and changes in relevant laboratory parameters are assessed.

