#### Statistical analysis

A detailed analysis plan is drawn up prior to the analysis.**Baseline comparability**: Patients in each treatment group in each site are described separately with respect to baseline characteristics. The clinical importance of any imbalance will be noted, though statistical tests of significance are not undertaken.**Primary analyses**: The primary analysis of the study is the assessment of therapeutic equivalence of the 4 treatments (clinical non-inferiority) with respect to therapeutic success at day 63 and their safety throughout the follow-up, i.e. up to one year after delivery.

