#### Patients follow up

Scheduled visits are at day 3, 7 and then every week until day 63 post-treatment. However, women are encouraged to attend the antenatal clinic if they felt ill between scheduled visits. At the end of the active follow-up period, women are asked to attend the antenatal clinic monthly and at any time they feel unhealthy until delivery. At each visit, scheduled and unscheduled, the medical history since the last visit (including any treatment taken), current signs and symptoms (if any) are collected. A blood sample for thick and thin blood film and later genotyping to determine the rate of re-infection is collected and the body temperature checked. Haematology (Hb, total white blood cell count, differential count) is measured at day 7, 14, 28 and 63; biochemistry (total bilirubin, ALAT and creatinine) at day 7 and 14.

If pregnant women recruited during the third trimester deliver before the end of the 63-day active follow, scheduled visits continue after delivery until the day 63 is completed. The outcome of pregnancy, including any congenital abnormality, the birth weight and maternal Hb are collected as soon as possible after delivery. In addition, a placenta impression smear and a placenta biopsy for later histopathological analysis are collected. Both the mother and the new-born are reassessed twice after delivery for any adverse event: between 4 and 6 weeks and then after one year (Table 3). Antimalarials or antibiotics with antimalarial activity (erythromycin or other macrolides, co-trimoxazole or other sulphonamides, any tetracycline including doxycycline, and quinolones, clindamycin) cannot be administered during the active follow up as it would lead to withdrawal of the patient from the study.

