**Table 3 Tab3:** **Study procedures/study visit schedule**

Day	0	1	2	3	7	14	21	28	35	42	49	56	63	Any other day ^1^	Delivery	4-6 weeks post-partum	EPI clinics	1 year post-partum
History (symptoms)	X																	
Informed consent	X																	
Examination (clinical)	X	X	X	X	X	X	X	X	X	X	X	X	X	X	X			
Foetal viability	X			X	X	X	X	X	X	X	X	X	X	X				
Blood Pressure	X	X	X	X	X	X	X	X	X	X	X	X	X	X	X			
Temperature	X	X	X	X	X	X	X	X	X	X	X	X	X	X	X			
Blood film	X	X	X	X	X	X	X	X	X	X	X	X	X	X	X			
Filter paper PCR	X				X	X	X	X	X	X	X	X	X	X	*X* ^2^			
Adverse events	X	X	X	X	X	X	X	X	X	X	X	X	X	X	X			
Concomitant medications	X	X	X	X	X	X	X	X	X	X	X	X	X	X	X	X		
Hb	X				X	X		X		X			X		X			
Haematology	X				X	X		X					X		X			
Treatment	X	X	X															
Blood sample for PK					X													
Pop PK	3 samples/woman according to a predefined schedule (120 women in 3 sites each)																	
*In vitro* test	X	and time of recurrent infection																
Biochemistry	X				X	X		X^3^					X^4^					
Placenta sample															X			
New born assessment															X	X		
Infant assessment																	X	X

^1^Spontaneous attendance to the health facility.

^2^Includes placental blood sample.

^3^Only ALAT and total bilirubin.

^4^Only ALAT and total bilirubin, and only if abnormal at Day 28.

Patients with treatment failure, including parasitological failure, are treated with rescue treatment (quinine 10 mg/kg orally three times a day for 7 days or an anti-malarial treatment according to the country’s national guidelines) and their active follow up stopped. Nevertheless, they are still followed up (safety data) until one year post-delivery.

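### The primary safety endpoint is given incompatible time windows (63 days, or up to one year after delivery), and the visit schedule does not support the longer one for mothers

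*Protocol article*

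**What the plan says.** Safety is one of two primary endpoints. The protocol article gives its time span in several places:

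- Primary endpoint, safety profiles: "Subjects are monitored for 63 days for possible development of adverse events".
- Trial objectives and purpose: "incidence of adverse events until one year post-partum".
- Study design, below Table 1: the primary analysis covers efficacy at day 63 and "their safety throughout the follow up, i.e. up to one year after delivery". The Statistical analysis section repeats this: "their safety throughout the follow-up, i.e. up to one year after delivery".
- Patients follow up: mother and new-born are "reassessed twice after delivery for any adverse event: between 4 and 6 weeks and then after one year", with a pointer to Table 3.
- Table 3: the row "Adverse events" is marked at the 13 day columns, at unscheduled visits and at delivery. It is blank at 4–6 weeks post-partum, EPI clinics and one year. The only entry in the one-year column is the infant assessment.

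The Safety section under Statistical analysis compares any AE, any SAE and any drug-related SAE between arms by Fisher's exact test, in all treated patients.

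**The concern.** A primary endpoint needs one time window. Here the endpoint definition gives one and the primary analysis another. The proportion of women with any AE or any SAE grows with the length of observation, so the same test on the same women can give different answers at day 63 and at one year. The trial is open-label, so a window settled late is open to challenge.

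There is also a data-collection gap. The primary analysis as worded needs maternal events up to a year after delivery, but the schedule marks no maternal adverse-event assessment after delivery. Events from that period could be under-recorded in every arm.

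Finally, a long window adds events unrelated to a three-day treatment, which can make an early difference between arms harder to detect.

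**Working it through.** **The texts side by side.** The definition says 63 days. The objective and both statements of the primary analysis say one year after delivery. The AE row of the schedule ends at delivery, while the follow-up text adds two post-partum assessments. In the same table the concomitant-medication row does continue to 4–6 weeks, so the blank AE cell there does not come from a missing visit.

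**The protocol's own safety figure.** The Sample size section claims 90% power for major adverse events at a frequency of at least 2–3%, without a comparator rate, significance level or window, so it cannot be uniquely reproduced. With 870 against 870 and two-sided 5%, a 2-point excess has 93% power at a 0.5% background and 85% at 1%. A 3-point excess has 93% at 2% and 86% at 3%. The claim therefore fits only a low background, and a longer window raises the background.

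**Length of the long window.** Enrolment is at 16 to under 37 weeks' gestation. Assuming delivery at 40 weeks, one year after delivery is (40 − 37) + 52 = 55 weeks to (40 − 16) + 52 = 76 weeks from treatment. Against 9 weeks (63 days) that is 55/9 = 6.1 to 76/9 = 8.4 times as long.

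**Effect on power.** The document gives no event rates, so all risks below are assumptions. Let pC and pT be the day-63 risks in the two arms, W the window in weeks, and c the later hazard, common to both arms, as a fraction of the control arm's 63-day hazard.

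- Later event-free probability: S = (1 − pC)^(c(W − 9)/9)
- Risks by the end of the window: 1 − (1 − pC)S and 1 − (1 − pT)S, so the difference is (pT − pC)S
- Power: Φ[(d − 1.96·se0)/se1], where d is the difference, n = 870 per arm, se0 = √(2p̄(1 − p̄)/n) with p̄ the mean risk, and se1 is the unpooled standard error

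Example: 40% against 50%, W = 55, c = 1. S = 0.6^(46/9) = 0.0735. The risks become 95.6% and 96.3%, the difference falls from 10 to 0.73 points, and power is 12%.

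| Day-63 risks | Power, day 63 | c = 1: risks at 55–76 weeks | c = 1: power | c = 0.25: power |
|---|---|---|---|---|
| 40% v 50% | 98.8% | 95.6–98.7% v 96.3–98.9% | 11.9–6.2% | 67.1–50.4% |
| 20% v 28% | 97.5% | 74.4–84.8% v 77.0–86.3% | 23.7–14.5% | 71.8–59.6% |
| 2% v 5% | 92.6% | 11.6–15.7% v 14.3–18.3% | 39.0–29.9% | 73.1–65.3% |

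In the first two rows the difference itself shrinks. In the third it stays near 2.6–2.7 points, and power falls mainly because the background rises. Fisher's test is slightly less powerful than this approximation: simulated power for 2% against 5% is 92%.

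**The case against.** The strongest defence is that the protocol describes two tiers: 63 days of active follow-up, then longer safety follow-up. Women with treatment failure leave active follow-up but stay in safety follow-up to one year after delivery, which fits that reading, and the sentence about 63 days does not expressly limit the analysis. This explains why two durations appear. It does not say which is primary, because the one-year span is written into the primary analysis itself, and it does not explain the AE row in Table 3.

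A second defence is that the analysis plan, which is not shown, may fix the window. It is fair that the silence of the Fisher-test paragraph on timing is no fault in a protocol. But a plan that chose either window would still contradict part of this text.

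Third, the long window has a purpose. Congenital anomaly counts as an SAE, and women enrolled before 31 weeks (40 − 9) would deliver after day 63 if they reach 40 weeks. This stands, and it is a reason to keep the long follow-up.

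A reader might infer that a one-year analysis would drive any-AE risk to nearly 100% and hide real drug differences. The document does not support that. It gives no rates. In the 20% v 28% case the risks reach only 74–86%. A constant later hazard is doubtful when visits go from weekly to monthly and then to two post-partum contacts. The separate drug-related SAE comparison and the coded tabulation also limit dilution, although relatedness is judged by the reporting investigator in an open-label trial and that comparison covers SAEs only.

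Nor does the gap in Table 3 show uneven capture between arms: all arms share one schedule, so it points to under-recording overall. The abstract's shorter description of maternal follow-up is a visit summary and adds little.

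**Conclusion.** The contradiction holds and concerns a primary endpoint: 63 days in the definition, one year after delivery in the objective and primary analysis, and an AE schedule that ends at delivery despite text promising two later assessments. It should be corrected, because both the data collected and the result of the any-AE and any-SAE tests depend on it.

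The loss of power is a possibility, not a demonstrated harm. Its direction is clear in every case tried, but its size rests on assumed event rates, a common later hazard in both arms, delivery at 40 weeks and all 870 women per arm observed throughout. Under those assumptions power of 93–99% at day 63 becomes about 6–39% with an equal later hazard and about 50–73% with a quarter of it. The long follow-up is not itself a mistake.

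**What to change.** - Reconcile Trial objectives, Study design, Primary endpoint, Statistical analysis, Patients follow up and the AE row of Table 3.
- Name one window for the primary maternal AE/SAE comparison. Day 63 matches the endpoint as defined; if one year is intended, the definition must change instead.
- Report delivery outcomes, birth defects, later maternal SAEs and infant outcomes to one year as separately named safety endpoints, so that the long follow-up is kept.
- Mark in Table 3 the post-partum adverse-event assessments that the follow-up text already states, and say whether each concerns the mother, the child or both.

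The cost is wording and table alignment, with no visits beyond those already described. The downside is that later events leave the single pooled comparison and are reported separately. Since the article reports data collection as complete, the window should be fixed before the arms are compared, and the report should say how many mothers had a recorded adverse-event assessment after delivery.
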